### ^Data collection^

Data is collected using an electronic case report form, and the data types, collection processes, and entry processes were jointly developed by the PROMISE group to ensure all participating institutions and functional areas are working to the same standard.

Data is recorded and stored pseudonymized in a central electronic database at a specialized interdisciplinary center. During the trial, the investigators and trial site staff receive system documentation, training, and support for the use of the database. Time-point specific questionnaires and forms are completed by the patient, or the attending physician/physiotherapist, or both.

Data collection points (Table) are:
baseline visit,1 week before surgery,day of surgery,hospital discharge,rehabilitation center discharge,3 months (±2 weeks) after hospital discharge,6 months (±2 weeks) after hospital discharge,12 months (±2 weeks) after hospital discharge,and 12 months (±4 weeks) after hospitalization (clinical follow-up).

Baseline data includes age, sex, comorbidities, initial diagnosis according to International Classification of Diseases (version 10), and socioeconomic data. The other collected data includes:
hip disability (HOOS),knee disability (KOOS),patient health quality (PHQ-4/SSD),quality of life (EQ-5D-5L),social support (Oslo Social Support Scale [OSSS]),personal expectations (Hospital for Special Surgery [HSS] score),rehabilitation success (Staffelstein score),and optimism/pessimism (Life Orientation Test-Revised [LOT-R]).

### ^Data quality assurance^

On-site qualified study nurses ensure that all personnel understand the trial and follow its protocol, including adhering to the standardized surgery and postoperative procedures. Surgeries are performed at centers that are qualified for the Enhanced Recovery process. A steering committee supervises the trial progress and provides guidance to all participating treatment groups.

Furthermore, the electronic database includes an interface to import quality-assured data that is sent by the participating hospitals to the Institute for Quality and Patient Safety.

### ^Estimated sample size and power^

The estimated sample size is based on the primary endpoint (chronic pain at 12 months), which will be evaluated using a 2-sided binomial test. A previous report has indicated that approximately 9% of patients report chronic pain after 1 year (Beswick et al. 2012). Thus, 1,900 patients are required to detect a 20% reduction (i.e., from 9% to 7.2%) based on an α level of 5% and power of 80%. Assuming 5% of patients will be lost to follow-up, the target sample size is 2,000 participants. This sample size also provides power of > 80% for analyzing the 2 confirmatory secondary endpoints (number of anemia cases and physical activity after 1 year; values selected from the literature), which will be analyzed only if a significant improvement is observed in the primary endpoint.

The secondary analyses are based on non-inferiority tests and previously reported values. The number of anemia cases will be tested to determine whether it is ≤ 2% below the expected reference value of 15.5% for Central Europe (McLean et al. 2009). Physical activity will be tested using the HOOS-PS/KOOS-PS to determine whether the patients achieve at least the minimum clinically important improvement (23 points) (Paulsen et al. 2014). To comply with the α-error, confirmatory testing for these 2 secondary endpoints will be performed only if statistically significant improvement is observed for the primary endpoint. To evaluate the achievement of a plateau in the number of interactions between care partners, the implementation period is divided into 3 intervals. The number of interactions in intervals II and III will be tested for equality. The criterion for equality will be based on the difference between the 1st and 2nd intervals. Poisson models will be used to compare the numbers of healthcare interactions between PROMISE participants and the control group, with sub-analyses according to different cost categories (e.g., hospital stays vs. general practitioner visits). Factors that potentially influence healthcare utilization, interactions, and quality of life will be evaluated using hierarchical regression models with care partners considered as clusters.

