## ^Patients and methods^

### ^Study design^

The PROMISE trial is a prospective multi-center mixed-method study, including patients with an indication to undergo surgery (THA or TKA) at 3 German hospitals (a regional hospital, an orthopedic-specialized hospital, and a tertiary referral university hospital). The PROMISE process involves standardized indication criteria for intervention (Schmitt et al. 2017), preoperative screening for psychological (Gylvin et al. 2016) and geriatric risk factors (Gronewold et al. 2017), blood management (Vaglio et al. 2016), preoperative patient education (Edwards et al. 2017), no preoperative fasting (Smith et al. 2011), postoperative nausea and vomiting prophylaxis (De Oliveira et al. 2013), maximum soft-tissue-sparing techniques (Ljungqvist et al. 2017), intraoperative bleeding and swelling management (Guler et al. 2016, Nielsen et al. 2016), avoidance of suction drainage (Kelly et al. 2014), bladder catheters (Huang et al. 2015), and intravenous catheters (Sharma et al. 2010), local infiltration analgesia (Yun et al. 2015), multimodal oral pain therapy (Khan et al. 2014), starting rehabilitation on the day of surgery (Okamoto et al. 2016), functional discharge criteria (Hansen 2017), and intensified rehabilitation (DRV 2016). All patients are followed for up to 12 months after surgery. Data are collected by medical staff at the time of examination on indication, during patient education, at surgery, at hospital discharge, at the end of rehabilitation, and at 12 months after surgery. Patient-reported outcome measurements are obtained before surgery, at hospital discharge, and at 3 months, 6 months, and 12 months after surgery. Regarding secondary endpoints, a control group will be used consisting of patients from a German health insurance database. Patients will be matched according to age, sex, and diagnosis. To limit the number of survey-based instruments and patient burden, we conducted guideline-based interviews with 10 randomly selected patients to identify aspects that are difficult to capture using a quantitative approach. Interviews have been also conducted with different care partners (e.g., physicians and physiotherapists) to identify and address potential burdens.

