### ^Preoperative screening for concomitant previous conditions^

Anemia is identified using the laboratory values for hemoglobin, ferritin, transferrin saturation, blood cell counts, red blood cell morphology, glutamic pyruvic transaminase, glutamic oxaloacetic transaminase, bilirubin, C-reactive protein, and reticulocytes. If necessary, iron is administered (orally or intravenously). Screening is performed to identify seniors at risk (ISAR screening) and psychosomatic risk (Patient Health Questionnaire-4 [PHQ-4], Oslo Social Support Scale [OSSS], Somatic Symptom Disorder [SSD], Life-Orientation-Tests [LOT-R]). Preoperative screening for thrombosis and bleeding risk is based on previous deep vein thrombosis or pulmonary embolism, known coagulation disorder/thrombophilia, venous thromboembolism in immediate relatives, previous severe bleeding, cancer within the last 5 years, and varicose veins. Specialized co-care is permitted if required.

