#### Secondary endpoints

The secondary endpoints are number of recognized pre-existing conditions (as proxy we use pre-existing anemia) at baseline, physical activity at 12 months after surgery, use of medical services during the 12 months after surgery, quality of life at 12 months after surgery, and interactions between care partners during the 12 months after surgery. Physical activity is evaluated using the HOOS/KOOS subscore HOOS-PS/KOOS-PS (physical function short form) for THA/TKA cases, with data collected before the surgery and at 3 months, 6 months, and 12 months after the operation. Quality of life at 12 months after surgery is assessed using patient-reported scores from the EQ-5D-5L (Conner-Spady et al. 2015) and the EQ-5D visual analogue scale (VAS) on a 0–100 numeric scale. This data is also collected before surgery and at 3 months, 6 months, and 12 months after surgery.

Type and frequency of use of medical service during the 12 months after surgery is evaluated using a questionnaire. The results will be compared with results from a control group of patients from a German health insurance database who are matched according to age, sex, and diagnosis/treatment history. Statistical power for those analyses will be improved by matching 1 PROMISE participant to 4 control individuals. Cost analyses will also be performed to compare the PROMISE and control groups, to identify potential savings. Interactions between care partners during the first 12 months after surgery are also considered to determine whether a stable plateau is reached in the number of intersectoral interactions for each patient. The interviews will be evaluated according to the qualitative content analysis described by Mayring (2000).

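### The confirmatory anemia test sets one cohort proportion against a fixed 15.5% and so cannot separate recognition of anemia from its prevalence in the enrolled patients

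*Protocol article*

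**What the plan says.** - **Endpoint.** The section on secondary endpoints lists the "number of recognized pre-existing conditions (as proxy we use pre-existing anemia) at baseline". The construct is recognition; anemia stands in for the wider set of conditions.
- **Test.** The section on estimated sample size and power makes the number of anemia cases one of two confirmatory secondary endpoints, tested only if the primary endpoint improves significantly. It states that "The secondary analyses are based on non-inferiority tests and previously reported values", and that the anemia count is tested for "whether it is ≤ 2% below the expected reference value of 15.5% for Central Europe".
- **Power.** The same section claims that "This sample size also provides power of > 80% for analyzing the 2 confirmatory secondary endpoints".
- **Ascertainment.** Under preoperative screening, "Anemia is identified using the laboratory values for hemoglobin, ferritin, transferrin saturation" and further markers. The data collection table places this assessment 1 week before surgery, so it is part of the PROMISE process.
- **Comparator.** The study design section says "Regarding secondary endpoints, a control group will be used", drawn from an insurance database and matched on age, sex and diagnosis. The anemia test uses the literature value instead. The discussion says that published results serve where direct comparison with controls is not possible.

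**The concern.** A claim about recognition needs either a denominator of truly anemic patients or a recognition rate under usual care. The test has neither. It counts anemia cases in one cohort and compares the proportion with a regional reference value, so the result depends on who was enrolled as well as on how well the process detects anemia.

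The error can go either way. A cohort with little anemia can fail although every case was found. A cohort with much anemia can pass although many were missed. If the primary endpoint succeeds, the trial would then make or withhold a confirmatory statement about recognition for reasons that may have nothing to do with recognition.

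**Working it through.** **Inputs from the protocol article:** reference 15.5%; margin 2% (absolute or relative not stated); 2,000 enrolled and 1,900 evaluable for the primary endpoint; 5% alpha, two-sided for the primary endpoint. The sidedness of the non-inferiority tests is not stated. Anemia is a baseline measure, so n = 2,000 is used below unless noted.

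**Step 1. Reproduce the stated power.** With an absolute margin, the null bound is 15.5% − 2% = 13.5%. The test rejects p ≤ 13.5% in favor of a higher proportion, with true p = 15.5%.

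Normal approximation for 80% power: n = [z(1−α)·√(0.135 × 0.865) + 0.8416·√(0.155 × 0.845)]² / 0.02².
- One-sided 5% (z = 1.645): n = 1,878.
- One-sided 2.5% (z = 1.960): n = 2,374.

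Exact binomial:

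| One-sided alpha | Cases needed, n = 2,000 | Power, n = 1,900 | Power, n = 2,000 |
|---|---|---|---|
| 5% | 296 (14.8%) | 79.4% | 81.4% |
| 2.5% | 301 (15.05%) | 69.2% | 72.0% |

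A relative margin gives a bound of 0.98 × 15.5% = 15.19% and power of only about 5% to 10%. The stated figure is therefore recovered with an absolute margin, one-sided 5% and a detected proportion of 15.5%. At the reference prevalence, that means every case is found.

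**Step 2. Separate the two components.** Detected proportion = prevalence × share recognized. P(pass) is the exact binomial probability of reaching the critical count at that proportion. The protocol article gives no prevalence for this cohort other than the 15.5% reference and no recognition share; all other values below are assumptions.

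| Prevalence | Share recognized | Detected proportion | P(pass), one-sided 5% | P(pass), one-sided 2.5% |
|---|---|---|---|---|
| 13% | 100% | 13.0% | 1.0% | 0.4% |
| 15.5% | 100% | 15.5% | 81% | 72% |
| 15.5% | 90% | 13.95% | 14% | 8% |
| 15.5% | 80% | 12.4% | 0.1% | <0.1% |
| 20% | 100% | 20.0% | about 100% | about 100% |
| 20% | 80% | 16.0% | 93% | 88% |
| 22% | 70% | 15.4% | 78% | 68% |

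**Step 3. Read the table.** With recognition fixed at 100%, moving prevalence from 13% to 15.5% to 20% moves the chance of success from 1% to 81% to about 100% (one-sided 5%). Complete recognition at 13% prevalence nearly always fails, while 70% recognition at 22% prevalence passes almost as often as complete recognition at 15.5%. Any result is compatible with many pairs of prevalence and recognition, and the test has no information to choose among them.

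**The case against.** A reader might infer that the test measures case mix and nothing else. The documents do not support that without a condition. At the reference prevalence the test reacts sharply to recognition: the pass rate falls from 81% to 14% when the recognized share falls from 100% to 90% (one-sided 5%). Only when everyone is laboratory-screened, as the screening section and data collection table plan, does the proportion reduce to prevalence. The false-pass rows need incomplete detection, and so departure from the planned process; the false-fail row does not and is the better supported of the two.

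A reader might also infer that 15.5% is a general-population value unsuited to arthroplasty patients. The article does not say which population or age group it covers. What can be said is that no adjustment to this cohort is described, and the confounding remains whatever the source.

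Nor is the use of a literature value a clear contradiction of the study design section. The control comparison is detailed only for service use and costs, and the discussion discloses the fallback to published results. That stands as disclosure, but it does not turn a cohort proportion into a measure of recognition.

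Finally, the endpoint is openly called a proxy and is tested only after a significant primary result. Anemia as proxy for other conditions is a separate matter from prevalence as proxy for recognition, and the ordering of tests controls alpha, not what the test means.

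**Conclusion.** The concern holds in this form: the confirmatory anemia test confounds prevalence with recognition and, under complete screening, reflects cohort prevalence only. Followed as written, it can yield an unsupported recognition claim or withhold a deserved one. At n = 2,000, an absolute margin and one-sided 5%, the chance of passing is 1% with full recognition at an assumed 13% prevalence, and 78% with 70% recognition at an assumed 22%. These scenarios illustrate the range and do not predict this cohort.

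The power statement does not answer the point. It is reproduced (81%) under the conditions in step 1, falls to 72% at one-sided 2.5%, and says nothing about recognition when prevalence differs from 15.5%. The primary endpoint is unaffected.

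**What to change.** 1. Remove the anemia comparison with 15.5% from the confirmatory sequence. Report the anemia proportion with a confidence interval, show 15.5% as descriptive context, and draw no conclusion about recognition from it.
2. As a supportive descriptive measure, report, among patients anemic at the laboratory assessment 1 week before surgery, the share not already listed among comorbidities at the indication visit. This is possible only if the comorbidity item captures anemia. The report should note that the item is patient-reported and collected about 7 weeks earlier (8 − 1), so recall and new-onset anemia are mixed with recognition.
3. Treat any comparison with anemia coded in the matched controls' insurance data as exploratory. Laboratory screening on one side and claims coding on the other would favor PROMISE by method of ascertainment alone.

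The cost is one confirmatory secondary claim; the physical activity test can remain in sequence after the primary endpoint. Items 1 and 2 change the analysis and reporting and need no new patient data. Item 3 depends on whether the insurer can supply anemia codes, which the protocol article does not show.

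### The gate on the primary endpoint does not by itself control the error rate between the two confirmatory secondary endpoints

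*Protocol article*

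**What the plan says.** All of this is in the Protocol article, section Estimated sample size and power.

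- The primary endpoint (chronic pain at 12 months) is one "which will be evaluated using a 2-sided binomial test", at an alpha of 5% with 80% power, for a fall from 9% to 7.2%. This needs 1,900 patients, raised to 2,000 for 5% loss.
- On the secondaries: "This sample size also provides power of > 80% for analyzing the 2 confirmatory secondary endpoints". The two are anemia cases and physical activity.
- Both are described as non-inferiority tests against published values. Anemia is judged against a reference of 15.5% with a 2% allowance. Physical activity is judged against an improvement of 23 points on the HOOS-PS/KOOS-PS.
- The multiplicity rule is that "confirmatory testing for these 2 secondary endpoints will be performed only if statistically significant improvement is observed for the primary endpoint". The same sentence gives its purpose as complying with the alpha error. The condition appears twice in the section, and each time it covers both endpoints together.

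The section states no order between the two, no division of alpha, no rule that both must succeed, and no significance level or sidedness for either secondary test.

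**The concern.** The article does more than leave multiplicity to another document. It names a mechanism and says what the mechanism achieves. A gate on the primary protects the secondaries only when the primary null is true, because the gate then rarely opens. The case that matters for the secondaries is the one the trial hopes for: chronic pain is truly reduced and the gate opens with probability of about 80% or more. Two confirmatory tests then stand side by side. If each is run at the full level, there are two chances of a false confirmatory claim, and the rule as written does nothing to limit them jointly.

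At stake is the standing of a confirmatory claim on anemia recognition or on physical function. The trial has one treatment arm and tests these endpoints against literature values. Anemia is assessed one week before surgery (data collection table), so those data exist long before 12-month function. An order chosen after seeing the anemia result would not be confirmatory.

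**Working it through.** **1. The plan's own figure.** One-sample binomial, normal approximation, p0 = 0.09, p1 = 0.072, two-sided 5%, 80% power:

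n = [1.960·√(0.09·0.91) + 0.842·√(0.072·0.928)]² / (0.018)² = 1,871.

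This is within 3% of the stated 1,900 (1,926 with a continuity correction). Exact power at 1,900 is 80.6%, and 1,900/0.95 = 2,000. The primary sample size is reproduced. The article gives no error rate for the secondary pair, so there is none to reproduce.

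**2. Error rate for the pair at 5% each.** Assumptions: the primary effect is real, there is no order or split, and both secondary endpoints lie exactly on their null boundaries.

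- Gate open, independent tests: 1 − 0.95² = 9.75%.
- Gate open, correlated test statistics (bivariate normal, one-sided): 9.3% at correlation 0.3, 8.8% at 0.5, 9.93% at −0.25.
- Ceiling under any dependence: 0.05 + 0.05 = 10%.
- Gate opening with the planned 80% power: 0.80 × 9.75% = 7.8%, with a ceiling of 0.80 × 10% = 8%.
- Primary null true: the gate keeps the error at or below 5%.

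**3. The same at one-sided 2.5% each.** Gate open, independent: 1 − 0.975² = 4.94%, with a ceiling of 5.0%.

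**4. Which level do the plan's figures suggest?** Read the anemia allowance as percentage points, so the null boundary is 15.5 − 2 = 13.5%, and take the true rate as 15.5%. Both are assumptions.

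Power = Φ{[0.02·√n − z·√(0.135·0.865)] / √(0.155·0.845)}

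| n | one-sided 5% | one-sided 2.5% |
|---|---|---|
| 1,900 | 80.4% | 71.2% |
| 2,000 | 82.1% | 73.3% |

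The claim of power above 80% is met at one-sided 5% and missed at 2.5%. If the standard error is instead taken at 15.5% throughout, power at one-sided 5% is 77.8% (n = 1,900) or 79.6% (n = 2,000). The check therefore favours 5% without proving it. No such check is possible for physical activity, because the article gives no standard deviation.

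**5. Off the boundary.** If the true anemia rate is 13.0%, the anemia test at n = 1,900 and one-sided 5% has an error of about 1.0%. The pair then gives 1 − 0.95 × 0.99 = 6.0%. The 9.75% is thus close to a worst case.

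**6. After a fix.**

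- Fixed sequence after the primary, each test at 5%: at most 5%. The endpoint placed first keeps its full level, so anemia placed first keeps 80.4%.
- Bonferroni split at 2.5% each: 4.94% if independent, at most 5%. Anemia power at n = 1,900 is 71.2%.
- Holm: at most 5%. Anemia faces 2.5% (71.2% power) unless physical activity has already been rejected, in which case it is tested at 5%.

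**The case against.** The strongest reply is that the article is condensed. It says when the two tests may be done, not that they are unordered or that each receives the full 5%. Order and split are commonly fixed in the full protocol or analysis plan. This stands as far as it goes: unordered testing at full level is the plain reading of one gate that opens both tests, but the article does not say so. It does not remove the point, because the article presents the gate itself as what satisfies the alpha error, and the gate alone does not.

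The second reply is that the only alpha stated belongs to the primary. With one-sided 2.5% for each secondary, the pair stays within 5%. That is correct, and it makes the inflation figures conditional. On the reading in step 4, though, the anemia power claim would then fail, so the section would still need a correction.

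Three stronger readings are tempting but unsupported:

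- A reader might take 9.75% as the maximum. It is the value for independent tests with the gate open; the ceiling is 10%.
- A reader might count HOOS-PS and KOOS-PS as separate tests and arrive at three. The article counts two confirmatory endpoints, and Secondary endpoints assigns the instrument by joint (hip or knee) within one physical-activity endpoint.
- A reader might apply the inflation whenever neither endpoint shows a benefit. These are non-inferiority tests: an anemia rate equal to 15.5% lies in the alternative, so a positive result there is not a false claim.

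**Conclusion.** The point holds in a limited form. The stated gate is not sufficient for the error control it is offered for, because it leaves the two confirmatory secondaries unprotected against each other once the primary succeeds. The error is 9.75% (independent tests, at most 10%) with the gate open, or about 7.8% at 80% primary power. These figures assume 5% per test, no order or split, and both endpoints on their null boundaries. The level is not stated. The anemia power claim fits one-sided 5% better than 2.5%, on an assumed percentage-point margin and a true rate of 15.5%, and that inference is sensitive to the variance used.

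A reader might infer that the trial's type I error control fails as a whole. The article does not support that: the primary test, its alpha and its sample size are untouched, and the error stays at or below 5% if the primary null is true. The matter is worth correcting but is confined to claims on two secondary endpoints.

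**What to change.** Before the secondary data are analysed, add a statement that gives:

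1. the significance level and sidedness of each secondary test;
2. a fixed sequence after the primary, in an order the sponsor chooses, with each test at the full level and confirmatory testing stopping at the first non-significant result.

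If the full protocol or analysis plan already fixes this, one clause citing it is enough.

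The cost is that the second endpoint is tested confirmatorily only if the first succeeds. Holm across the two avoids ranking them. However, its first step, like a Bonferroni split, puts anemia at 2.5%, with power of about 71% at n = 1,900. The statement of more than 80% power would then have to be restated. No change to the sample size or to data collection follows from the fixed sequence.

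### The plateau test takes its equality margin from the trial's own interval I–II change, so an always-stable process can hardly pass, while one still changing but slowing may

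*Protocol article*

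**What the plan says.** The protocol article lists interactions between care partners among its secondary endpoints. Its section on secondary endpoints gives the aim: "to determine whether a stable plateau is reached in the number of intersectoral interactions for each patient".

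The analysis appears in the section on estimated sample size and power. Implementation is cut into three intervals, and the second and third are compared to see whether their interaction counts are equal. How far apart they may lie is settled this way: "The criterion for equality will be based on the difference between the 1st and 2nd intervals".

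No multiplier, scale, minimum or maximum margin, significance level or named test accompanies this rule. The same section names two confirmatory secondary endpoints, anemia cases and physical activity. The plateau question is not one of them.

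**The concern.** An equality margin should say how much change between II and III is small enough to ignore. This rule makes that amount depend on how much changed earlier, which has two consequences.

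- If coordination between sectors works from the first interval, I and II are alike, the margin is close to zero, and no realistic II–III comparison fits inside it.
- If the early change is large, the margin is large, and a sizeable further change can fit inside it.

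The margin also carries sampling error that the rule does not mention. Interval II enters both the margin and the tested difference, so the two are correlated.

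At stake is whether the trial can say anything reliable about interactions settling down. Cross-sectoral coordination is a central aim, so immediate stability is a result the team would want to be able to show.

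**Working it through.** **The plan's own figure.** The article gives no margin, power or sample size for the plateau test. Its only derived size is for the primary endpoint, and that reproduces. With 9% against 7.2%, two-sided α 5% and power 80%:

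n = [1.960·√(0.09·0.91) + 0.842·√(0.072·0.928)]² / 0.018² ≈ 1,870.

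Exact binomial power at 1,900 is 80.6%, and 1,900/0.95 = 2,000. I use 1,900 only to set an interval size: 1,900/3 ≈ 633.

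**Assumptions not in the article.** 633 independent patients per interval; mean counts per patient μ₁, μ₂, μ₃ with Poisson variance; equality declared if the 90% confidence interval for the II–III difference lies within ± f × the observed I–II difference, that is

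|ȳ₃ − ȳ₂| + 1.645·√((ȳ₂ + ȳ₃)/633) < f·|ȳ₂ − ȳ₁|.

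The multiplier f is unknown, so I take 1, 0.5 and 0.25. The ratio-scale version replaces differences by differences of logarithms.

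**Stable from the start, 10/10/10.** The standard error of either difference is √(20/633) = 0.178, so the interval half-width is 1.645 × 0.178 = 0.292. The true margin is 0. To pass, chance alone must push |ȳ₂ − ȳ₁| above 0.292 plus whatever |ȳ₃ − ȳ₂| turns out to be. Both sides scale with the same standard error, so the pass rate barely depends on interval size or mean. It stayed near 1.7% at f = 1 for 100 to 2,000 patients per interval and means of 1 to 20.

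**Slowing change.** At the true means:

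- 20/10/5: difference 5, half-width 1.645·√(15/633) = 0.25. At f = 1 the margin is 10, and 5.25 < 10. At f = 0.5 the margin is 5, exactly the difference.
- 10/20/23: difference 3, half-width 1.645·√(43/633) = 0.43. At f = 0.5 the margin is 5, and 3.43 < 5.

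**Constant absolute pace.** The rule needs (ȳ₂ − ȳ₁) − (ȳ₃ − ȳ₂) to exceed 1.645·√(2σ²/n). That contrast has mean 0 and variance 6σ²/n, so with equal variances the pass rate is 1 − Φ(1.645·√(2/6)) = 1 − Φ(0.950) = 17%. With Poisson variances it is about 15% for 10/14/18 and 19% for 18/14/10.

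**Simulated share declared a plateau** (at least 200,000 trials per scenario):

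| True means I/II/III | Raw, f = 1 | Raw, f = 0.5 | Raw, f = 0.25 | Ratio, f = 1 |
|---|---|---|---|---|
| 10/10/10 | 1.7% | about 0 | about 0 | 1.7% |
| 10/10.2/10.2 | 11% | about 0 | about 0 | 12% |
| 20/10/5 | 100% | 13% | about 0 | 13% |
| 14/10/7 | 99% | about 0 | about 0 | 5% |
| 10/20/23 | 100% | about 100% | about 0 | 100% |
| 10/14/18 | about 15% | about 0 | about 0 | 99% |

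The last ratio-scale entry arises because a constant absolute rise is slowing in relative terms. ln(18/14) = 0.251 plus half-width 1.645·√((1/14 + 1/18)/633) = 0.023 gives 0.274, below ln(14/10) = 0.336.

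Change that accelerates on the raw scale (40% of the starting mean, then 60%) passes in about 0% on that scale. With three-fold overdispersion at f = 1 on the raw scale, 10/10/10 stays at 1.7%, 20/10/5 at 100%, and 14/10/7 falls to 84%.

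**If "equality" means only a point comparison**, |ȳ₃ − ȳ₂| < |ȳ₂ − ȳ₁|, both a stable process and a constant absolute pace pass in about 50%.

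**With a margin fixed in advance.** At a mean of 5, a stable process passes in 27%, 98% and 100% for margins of 0.25, 0.5 and 1.0 interactions. With a rate ratio required to lie within 0.80 to 1.25, 10/10/10 passes in 100%, and 20/10/5 and 14/10/7 in about 0%. 10/20/23 would still pass there: ln(23/20) = 0.140 plus half-width 0.020 gives 0.160, below ln 1.25 = 0.223.

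**The case against.** The article says the criterion is based on the I–II difference, not that it equals it. It is a condensed account, and the full protocol may set the multiplier, the scale and the test. This stands: the 100% and 99% figures for 20/10/5 and 14/10/7 belong to multiplier 1 on the raw scale and cannot be attributed to the plan. It does not remove the dependence on the data, which the article states as the rule. A smaller multiplier makes an always-stable process fail even more surely.

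It can also be argued that a plateau presupposes an initial change, so measuring flattening against that change is natural. That is a fair description of slowing. The stated aim, however, is stability, and a process can slow and still be changing substantially.

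A reader might infer that any steeply changing process would be declared stable. The documents do not support this. On the raw scale, change at an undiminished pace passes in about 15–19% at multiplier 1 (above the nominal 5%, but not usual), in about 0% at 0.5, and accelerating change essentially never passes.

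A reader might also see a conflict of clocks, because "Secondary endpoints" refers to the first 12 months after surgery while the analysis divides the implementation period. The two are compatible: 12-month counts per patient, grouped by the implementation interval to which the patient belongs.

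**Conclusion.** The point holds in limited form. The equality margin comes from the trial's own data, has no stated floor or cap, and shares interval II with the tested difference.

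The firmest consequence is that, under an equivalence test, a process stable from the start is declared a plateau in at most about 1.7% of trials for any multiplier up to 1, on either scale. This does not depend materially on interval size, mean count or overdispersion. It does depend on the test being an equivalence test; with a bare point comparison at multiplier 1 the answer is close to a coin toss.

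The other consequence is conditional. A process still changing substantially, but more slowly than before, can be called a plateau. How often depends on the unstated multiplier and scale, from about 0% to 100% in the scenarios shown.

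No efficacy claim or sample size rests on this endpoint, which lies outside the confirmatory hierarchy. The change is worth making but is not critical.

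**What to change.** State an equivalence margin for III versus II that does not use the I–II data, preferably as a rate ratio. Test it with two one-sided tests (90% confidence interval within the margin) from a count model that allows overdispersion. The same section already plans Poisson models for healthcare interactions, so this is a small extension. Report the I–II change descriptively.

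A range of 0.80 to 1.25 is only an example. It would accept a 15% further rise such as 20 to 23, and the team must decide whether that counts as stable. The margin also has to be justified against the expected precision: too tight a fixed margin fails a stable process too, as the 27% pass rate at 0.25 interactions shows.

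The cost is a sentence or two in the analysis plan and a team discussion to agree and defend the margin. Recruitment has closed, so the margin should be fixed before anyone looks at interaction counts by interval. No new data or patients are needed.
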